# Status-neutral community-based multilevel intervention to address intersectional stigma and discrimination, and increase HIV testing, PrEP, and ART uptake among YGBMSM in Ghanaian Slums: A clustered randomized control trial protocol

**DOI:** 10.21203/rs.3.rs-4486078/v1

**Published:** 2024-05-30

**Keywords:** HIV, Intersectional Stigma, Testing, Pre-Exposure Prophylaxis, Antiretroviral Therapy, Healthcare

## Abstract

**Background:**

While GBMSM constitute less than 2% of Ghana’s population, their HIV prevalence surpasses the national average by more than eightfold, emphasizing the critical need for targeted interventions to improve detection, care linkage, and reduce community transmission. This study seeks to increase HIV testing, Pre-Exposure Prophylaxis (PrEP), and Antiretroviral Therapy (ART) uptake (HPART) among YGBMSM through the adaptation of an evidence-based intervention (LAFIYA).

**Methodology:**

We will employ the ADAPTT-IT framework to adapt LAFIYA and evaluate its feasibility and effectiveness in addressing intersectional stigma and increasing HPART uptake among YGBMSM residing in Ghanaian slums. In aim 1, we will hold focus groups (n=5) and interviews (n=20) among YGBMSM and two FGDs among GBMSM-led organizations. At the HCF level, we will hold 6 FGDs and interviews (n=20) among nurses. In AIM 2, we will randomly assign 6 healthcare facilities (HCFs) to receive the LAFIYA (n=3) or wait-list control (n=3). Friend groups (cluster) of YGBMSM (N=240) will be assigned to receive LAFIYA (n=120) or a wait-list control (n=120). We will collect 3-, 6-, and 9-months post-intervention data among YGBMSM(n=240) and HCWs(n=300) to measure HPART adherence (primary outcomes), ISD reduction, HIV and status-neutral knowledge (secondary outcomes), and intervention acceptability, appropriateness, and feasibility (implementation outcomes).

**Conclusion:**

The intervention group will observe increased HPART adherence, reduced ISD, and enhanced HPART knowledge and efficacy relative to the wait-list control group. The findings will inform ISD reduction and HIV status-neutral implementation strategies – and place-based interventions that address access to HIV prevention and care among YGBMSM, slum and in different settings.

**Trail Registration:**

This study was registered on clinicalTrail.gov, with identifier number NCT06312514 on 03/14/2023. https://classic.clinicaltrials.gov/ct2/show/NCT06312514.

## Introduction

In Ghana, the HIV epidemic continues to pose significant public health challenges, particularly among gay, bisexual, and other men who have sex with men (GBMSM)^1–13^. Contributing to less than 2% of Ghana’s population, the HIV prevalence of this key population surpasses the national average by more than eightfold, emphasizing the need for targeted interventions to improve early detection, care linkage, and reduce community transmission^14–16^. Young GBMSM (YGBMSM) represent a vulnerable population that requires focused attention due to their increased HIV vulnerability^17–20^. YGBMSM aged 18 to 24 years comprise a sub-risk population within the broader GBMSM community, accounting for 63% of known HIV cases among GBMSM in Ghana^15^.

In addition to being young or GBMSM, living in urban areas, especially slums, can increase HIV vulnerability^21–23^. Slums house over 30% of Ghana’s urban residents, about 40% of our study area (Accra)^24,25^, and GBMSM in Accra have the highest HIV prevalence (44%) compared to nationwide GBMSM (18%)^26^. YGBMSM in slums remain at heightened vulnerability as slums remain documented high HIV-burdened areas due to structural issues (e.g., lack of access to care) and behavioral factors (e.g., transactional sex)^21–5,21,27–37^.

The advent of HIV self-testing (HIVST) and Pre-Exposure Prophylaxis (PrEP) alongside the established Antiretroviral Therapy (ART) represents significant milestones in the ongoing efforts to curb HIV incidence and enhance treatment adherence among diverse populations, including GBMSM^38–40^. HIVST facilitates repeated testing of self, partners, and clients^38^. The World Health Organization (WHO) recommends oral PrEP for persons with seronegative HIV tests at substantial and ongoing vulnerability to HIV. PrEP effectively prevents HIV acquisition but requires high adherence; adherence is the main predictor of effectiveness^39,40^. Studies in Ghana have reported low levels of knowledge but high acceptability of PrEP and HIVST among GBMSM^41–43^. Perspectives of policymakers in Ghana also indicate that HIVST is highly acceptable, but national guidelines and stakeholder consultations are necessary for successful implementation^44^.

Nonetheless, the uptake of HIV testing, PrEP, and ART (HPART) remains low among GBMSM in Ghana, with many researchers pointing to ISD as a key deterrent^42,45^. In Ghana, ISD towards GBMSM, particularly in the context of HIV, persists despite significant advancements in HIV awareness and advocacy^46,47^. GBMSM also face ISD due to legal, religious, and cultural antagonism, with 90% of Ghanaians against same-sex intercourse^16,48^. Existing evidence suggests a strong association between ISD and low HPART outcomes among this key population in the country^45,46,49–51^. At the intrapersonal level, GBMSM internalizes ISD experiences, develops guilt, shame, etc., and avoid HCFs^45,52–54^.

A mixed-method study in Ghana revealed that 62% of GBMSM respondents reported not testing for HIV in the past 12 months due to ISD^16,55^. Furthermore, our other previous work and others that engaged a section of YGBMSM as part of the generic GBMSM show that YGBMSM have challenges such as low HIV knowledge, ISD, and inadequate connection to care services^19,56–58^. Compared to adults, the ISD faced by YGBMSM also extends to engaging in preventative behaviors. Many cannot engage in HIV prevention conversations or be seen buying or holding a condom due to anti-premarital sex perceptions in Ghana^19,56–58^. Other studies have also reported low PrEP uptake and poor adherence to ART among this key population, with, among other things, stigma being a contributing factor^42,45^.

### The current study:

Behavioral interventions like the Many Men Many Voices (3MV) have shown efficacy in improving HIV outcome GBMSM^59–61^. Through its comprehensive approach, the 3MV intervention effectively empowers participants to make informed decisions about their sexual health, increase HIV testing rates, and adopt preventive measures such as condom use and PrEP^59^. Building upon the successes of the 3MV approach and to address the pressing need for an intervention tailored to the unique context of Ghanaian slums and the challenges faced by GBMSM, we piloted the LAFIYA HIVST intervention, which showed some effectiveness in improving HIVST among YGBMSM in slums. In this study, we seek to adapt our piloted Lafiya intervention further to incorporate a status-neutral framework, further enhancing its potential to increase HPART among GBMSM in Ghanaian slums. **LAFIYA, meaning “wellness” in Hausa,** is built upon the fundamental goal of promoting health and well-being. The LAFIYA intervention is a comprehensive program designed to address the ISD and improve HIVST among marginalized communities.

### Theoretical Underpinning

The study draws the Health Stigma and Discrimination Framework (HSDF) and scientific evidence from Ghana and SSA to postulate that stigmatized characteristics (sexual behavior, gender expression, age, and place) intersect with HIV stigma to impact HPART uptake and adherence among YGBMSM negatively^34,62–64^. The drivers and facilitators of ISD include gender norms, low HIV transmission, prevention and treatment knowledge, moral beliefs associated with HIV, and characteristics of persons (e.g., gays)^34,62–67^. ISD manifests through social exclusion, gossip, discrimination in HCFs, etc. It also manifests at the interpersonal level where YGBMSM stigmatizes other YGBMSM for gender expression or HIV status. At the intrapersonal level, YGBMSM can accept negative societal perceptions about GBMSM, PLWHIV, or slums and begin to blame themselves, develop self-doubts, etc.^34,62–64^. ISD can lead to increased risk behaviors and low HPART adherence, as internalizing the ISD forces YGBMSM to remain closeted and isolated. Thus, highlighting the importance of addressing the drivers, facilitators, and manifestations of ISD at YGBMSM and HCF levels and building the capacity at both levels (Figure1) to avert low HPART among YGBMSM^34,63,64^

#### Adapting LAFIYA, a multilevel ISD and HIV testing intervention, to a status-neutral intervention will increase HPART among GBMSM.

LAFIYA *refers* to a multilevel intervention that was developed through the adaptation of Many-Men-Many Voices (3MV). The 3MV remains the only CDC-recommended group evidenced-based intervention focused on influencing behavioral change to address the barriers to HIV prevention and care among Black GBMSM in the United States^68–71^. Our piloted LAFIYA, which is currently implemented at a larger scale through another grant, addresses Ghanaian YGBMSM contexts such as religion and ISD around HIV, sexual identity, and gender norms and expectations^2,72,73^. It also builds capacity for HIV self-testing (HIVST) by training YGBMSM on HIVST. At the HCF level, it trains selected anti-stigma nurses to offer linkage to care for YGBMSM who tested positive. Another study by members of our team also trained healthcare workers (HCWs) to offer ISD-free testing services^74^. Hence, combined, the two previously implemented interventions have begun to address ISD and HIV testing among GBMSM and HCF. But, both recruited HIV-negative GBMSM; none focused on PrEP uptake, and linkage to the care component was with selected providers (not the primary focus of the study). The proposed *LAFIYA* will address the drivers of ISD at YGBMSM and HCF levels, build a collaborative anti-stigma working relationship between GBMSM organizations and HCWs, and build capacity for 1) YGBMSM to self-initiate HPART 2) Providers to offer ISD-free status neutral HIV-care 3) Create social networks for continuous support.

## Methods

### Study design overview.

We aim to adapt and determine the preliminary efficacy of a multilevel status-neutral intervention (LAFIYA) to address HPART adherence among YGBMSM in Ghana’s slums using the following **aims. 1)** Adapt a multilevel intervention to address ISD and HPART using status neutrality among YGBMSM. **2)** Test the preliminary efficacy of the intervention to address ISD and increase HPART adherence using CRT. We will use the ADAPTT-IT framework as a guide to adapt LAFIYA^75^. The framework offers eight steps: (1) Assessment, (2) Decisions, (3) Adaptation, (4) Production, (5) Topical experts, (6) Integration, (7) Training, and (8) Testing. We will use steps 1 to 7 to implement AIM1 and the results from AIM1 to inform AIM2. Aim 1 will produce the intervention manual. AIM 2 will constitute the CRT phase, where we will assess acceptance, feasibility, and appropriateness of the intervention (**implementation outcomes**), the preliminary efficacy of the intervention to reduce ISD (**secondary outcomes**), and increase HPART adherence (**primary outcomes**) among YGBMSM.

### Study setting.

Accra, Ghana, the proposed study area, remains the primate city in Ghana, housing over 5 million people and about half of the urban population, 38% in Ghana^76–78^. Like other large cosmopolitan areas in SSA, Accra has the highest concentrations of slum communities, with half its population living in about 80 slums. About 20% of housing in Accra has an incomplete roof, yet 75% of such houses have inhabitants. About 32% of all housing in Accra consists of non-conventional structures (e.g., metal containers, wooden structures, kiosks)^78,79^. Accra also has the highest prevalence of HIV among SMM (44%) and part of the highest among the general population (3%), which is higher than the nations (2%)^80^.

### Preliminary Studies.

#### ISD experience among GBMSM and YGBMSM.

In our recent studies in Ghana^34,81^, we identified that GBMSM face various forms (e.g., experienced, anticipated, perceived, and internalized) of ISDs concerning sexual behavior or sexuality and gender expression **among their peers and healthcare workers (HCWs)**. HIV-related ISD continues to thrive due to the perception that contracting HIV signifies a punishment for sin and insufficient knowledge of HIV transmission. As such, GBMSM face insults, gossip, avoidance, and sometimes physical violence **from peers, the community, and HCWs**. In 2022, we found that over 70% of HCWs consider GBMSM mentally ill and non-Ghanaian. About 35% also said their co-workers/themselves were hesitant to care for GBMSM^81^. To circumvent ISD, many GBMSM **in slums prefer to travel outside or self-treat** as they avoid interacting HCWs, thus a need to combat ISD and increase HPART uptake. We consistently found similar results in several studies^13,34,62,64,73,74,81–89^.

#### HIV risk factors among YGBMSM.

We completed a 2022 formative study among **YGBMSM in Ghana’s slums** (Yale Fund for Lesbian and Gay Studies (FLAGS)). Qualitative interviews (n=15) show that YGBMSM have an increased HIV risk, e.g., inconsistent condom use and high transactional sex due to challenges with food insecurity. Some use sex work as their primary source of income. HIV knowledge was low, and HIV stigma was high. LAFIYA will address HIV/STD prevention knowledge gaps and reduce HIV ISD, especially age-group-specific HIV prevention needs of GBMSM youth.

#### Testing/self-testing among YGBMSM.

In 2022 (Yale Fund for Lesbian and Gay Studies (FLAGS). All interview participants (n-15) were not confident in HIV testing in slum HCFs but preferred GBMSM-friendly organizations^5^. As a follow-up, we conducted FGD with providers (n=9) who indicated that the main challenge in upscaling HIVST is the capacity to implement unassisted HIVST. In PRISM (NINR/R01NR019009), data from 10 GBMSM interviews and 8 FGDs showed: **Experiences:** 1) fear of HIV infection created a stressful HIV testing experience, and 2) friendly and supportive healthcare environment facilitated a positive experience in healthcare facilities. **Motivators or facilitators:** 1) understanding that HIV testing is an HIV prevention strategy; 2) encouragement from friends and peers; 3) understanding risk associated with sexual behaviors such as transactional sex 4) education or information on HIV; 5) access to free testing and incentives; 6) early symptoms and provider recommendation. **Barriers:** 1) negative community perceptions of HIV, 2) individual-level low-risk perception or indifference about HIV infection; 3) location and cost; 4) inadequate testing availability; 5) ISD at HCF.Thus, if we combat ISD at both HFCs and peer levels and build capacity for HPART, YGBMSM will use the services and improve their health outcomes^90–92^.

#### PrEP uptake among YGBMSM.

PrEP uptake and retention remain challenging among GBMSM Ghana**, but no PrEP intervention has been tested in the country**. Hence,we held a focus group discussion with current and previous PrEP implementing partners (7 gay and bisexual self-identified program implementers and 3 healthcare workers) to evaluate the factors affecting the initiation and continuation of PrEP. We found that **individual-level elements**, e.g., fear of PrEP side effects, the ISD associated with taking PrEP, challenges with daily medication use, and fear of HIV testing procedures, affected PrEP initiation. At **the community level**, the ISD associated with HIV impacted the interest of potential PrEP mentors to take the lead in PrEP promotion. **Implementation-level factors** include ISD from HCWs, lack of decentralized PrEP support, and target-focused implementation programs that failed to cultivate sustained PrEP understanding and uptake. Before the PrEP introduction in Ghana, FGDs conducted by our team members among GBMSM showed low knowledge of PrEP. However, once information about PrEP was provided, there was high acceptability^13^. The primary reason for acceptability was that PrEP offered extra protection against HIV. Our recent focus group under PRISM showed the same results. LAFIYA will increase education, support, and behavioral change for PrEP uptake and retention for YGBMSM instead of focusing on enrollment numbers.

**Linkage to care.** In Accra, our team conducted qualitative studies with GBMSM adolescents and adults living with HIV in 2015 (CFAR/NIH-P30 AI078498), (n=30) and 2021 (NINR/R01NR019009) (n=10). In 2015, **barriers identified include fear of being seen in HIV HCFs** and long wait times.

Motivators/facilitators included social support, HIV treatment knowledge, and positive experience from HCW^93^. In 2021, the identified barriers include community and HCF-level ISD, confidentiality issues, alternative medicine such as herbs and churches, and substance use. Motivators/facilitators included positive experiences with HCW, HIV counseling, and detailed medication information. Our 2021 quantitative analysis of 225 GBMSM living with HIV, supportive healthcare climate (OR ¼ 1.63, p < .01), vicarious HIV stigma (OR ¼ 2.73, p < .01), and age (OR ¼ 1.06, p < .004) predicted care. Conversely, HIV stigma negatively predicted care (OR ¼ 0.65, p < .05)^94^. These findings highlight the need for interventions that address linkage to care issues, especially disinformation and misinformation among GBMSM and healthcare providers. The status-neutral care will present an innovative care delivery medium, affirming and competent healthcare providers to improve care and eliminate factors (e.g., alternative medicine use and ISD.

### Aim 1: Adapt a multilevel intervention to address ISD and HPART using status neutrality among YGBMSM

#### ADAPT- ITT, Step 1 (Assessment).

We will conduct FGDs and in-depth interviews (IDI) with YGBMSM and GBMSM+NURSES providers to deepen understanding of ISD, barriers, and facilitators of HPART adherence among YGBMSM. We will integrate realities from both providers and YGBMSM to optimize the intervention potential to address ISD and increase HPART. FGDs have demonstrated suitability in studies of sexual health and capitalize on spontaneous conversational interaction in the group. IDIs have proven successful in allowing in-depth openness about perspectives on issues of a private nature^84,95,96^. We will examine the following.

#### YGBMSM.

**1)**Evaluate experiences of ISD (e.g., HIV, place, age, sexual) and HIV testing, prevention, and care and how such experiences influence HPART decisions. **2)**Assess knowledge of HIV, prevention options, willingness to test, and preferred means of ART initiation or HIV prevention after testing. **3)** Identify feasible options for engaging with testing (self-testing, home, HCF, etc.), PrEP, and ART medication, as some YGBMSM may live in shelters and face privacy challenges. **4)**Solicit recommendations for combating ISD and increasing HPART adherence. **Providers. 1)**Assess experiences with implementing HPART to YGBMSM. **2)**Assess the role of ISD and other facilitators and barriers to HPART implementation among YGBMSM. **3)**Garner updated information on implementing anti-ISD interventions in HCFs and sustainability practices over time to inform aspects of the intervention. **3)**Solicit recommendations for combating ISD and increasing HPART adherence.

### Sampling and recruitment

#### Technique: YGBMSM FGDs and IDIs:

We will combine venue and chain referral techniques to YGBMSM^97^. We have used both strategies independently in previous studies; however, integrating both will allow us to optimize reach as YGBMSM in Ghana remain hidden^34,98^. Here. The community partners will contact YGBMSM through their outreach services and invite them to participate in the study. We will then ask YGBMSM who consent to the study to refer other YGBMSM known to them. We will interview 20 YGBMSM living with HIV and include 8 to 10 persons, regardless of HIV status, in each FGD (n=5).

**GBMSM civil society organizations FGD:** we will use the purposive sampling technique to recruit 8–10 for each FGD (n=2)^99,100^. Here. We will invite participants due to their specific abilities to provide unique and in-depth information necessary to answer the research questions. This sampling method remains best for our process, considering YGBMSM in Ghana remains hidden due to ISD. The providers’ identities remain confidential and only known to the team and other GBMSM because of previous training and their roles in providing care to GBMSM in the country.

**HCF staff: A total of 6 peer-led nurses**, one from each facility, will be selected by the Ghana HIV/AIDs program to assist research assistants in recruiting staff that represents a diverse cross-section of the facility whom YGBMSM are likely to encounter during the process of HPART initiation or adherence (e.g., receptionist, security guard, nurse, HIV counselor, cashier). Each FGD (n=6) will include 8–10 persons stratified by clinical vs. non-clinical. We will secure an updated list of HCF staff and construct a random sample that will be contacted from the list while allowing staff to decline participation confidentially. The peer-led nurses will perform the liaison role throughout the study period. **Anti-ISD Trained Nurses IDIs**: We will also use the purposive sampling technique for anti-ISD nurses (n=20) who were trained as facilitators under our previous works in Ghana (LAFIYA and PRISM)

#### Sample size justification.

We are ensuring a sample size of at least 20 for each activity as it equals or exceeds other standard IDIs conducted among SSM and providers^34,98^. It’s also within the standard recommended for qualitative studies (n=19)^117^. Thus, it will allow for comprehensive coverage of necessary information to reach saturation and provide enough information to inform the next study stage.

### Inclusion and exclusion criteria.

#### YGBMSM FGD and IDI:

To be eligible for FGD, the person must be between 18 to 25 years old, currently identifies as a cis-gender man, have had sex with another man within 8 months before engaging with the recruitment team, and must reside within a slum community in the Accra metropolitan areas. To be eligible for IDIs, participants must self-disclose living with HIV. **GBMSM civil society organizations FGD.** The person must have experience providing GBMSM with HIV prevention and care services for at least one year. Must reside in Accra metropolitan area. **HCF staff** FGDs: HCF staff are eligible to participate in the FGDs if employed at a study-participating facility. **Anti-ISD Trained Nurses IDIs** HCF staff are eligible to participate if they are trained in our previous interventions and have previously delivered them in a Ghanaian HCF.

### Data collection.

#### YGBMSM.

Trained GBMSM collaborators who collected data in our previous studies with YGBMSM in Ghana will collect the data. **Providers:** Trained GBMSM+NURSE collaborators will collect provider data. The collaborators will conduct and audio record all interviews privately to ensure privacy. They will also translate interviews where the language is not English; the PI and GBMSM+NURSE team leaders will verify such translations for accuracy. For example, the PI is fluent in northern Ghanaian languages, and the team leaders are fluent in southern Ghanaian languages. We expect participants to be mixed due to the nature of slums. As such, our data collection team is combined with individuals who reflect the diversity of the participants. The recordings will then be encrypted and uploaded to the team box folder, accessible only to key personnel.

#### Data analysis.

We will use Dedoose Software to analyze the qualitative data in two phases to 1) Identify areas and content for adapting the intervention and 2) publish study findings.

**For intervention adaptation**, we will use a summative analysis process. We will form an 8-member team consisting of GBMSM+NURSES data collectors, a sample of participants, and research content experts (PI and site PI), led by a qualitative expert (Co-I, [name]) to review and provide critical summaries of key findings from the IDIs. Two investigators will review each transcript to ensure we establish the reliability of the information extracted and discuss conclusions and meanings of unclear messages in the team meetings. [name] and [name] will then systematically combine the summaries by identifying major points from each summary that address the drivers and manifestations of ISD, HPART experiences, options for implementing HPART, barriers and facilitators to HPART implementation, and recommendations for factors to be considered in the intervention to address ISD and upscale HPART. GBMSM+NURSES, who conducted the interviews, will review the final summaries to ensure they are consistent with their understanding and realities of the YGBMSM and HCWs interviewed. Their views will be discussed, and any corrections will be agreed upon at the team meetings to finalize the findings.

**For manuscript development**, we will conduct a more detailed qualitative content analysis. In this procedural approach, we will categorize and review data iteratively to generate conclusions based on the text’s explicit and implicit meaning. Led by [name], with support from [name], [name], [name], [name], and GBMSM+NURSES in Ghana, we will use open coding to identify categories and create a thematic codebook from the transcripts. The coders will independently apply the codebook generated to a sample of transcripts (4 each for YGBMSM and provider transcripts). They will meet to review line-by-line coding, discuss discrepancies, and review and update the codebook to ensure consistency in coding. They will then divide the remaining transcripts and independently code them using the finalized codebook. Code excerpts will then be exported from Dedoose for consolidation to answer the research questions.

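### Participants may join the interview review team before summaries are pooled, which could reveal an interviewee's HIV status to a peer

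*Protocol article*

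**What the plan says.** The Aim 1 *Data analysis* section describes two analyses of the qualitative data. For adapting the intervention it states: "We will form an 8-member team consisting of GBMSM+NURSES data collectors, a sample of participants, and research content experts". The team's task is "to review and provide critical summaries of key findings from the IDIs". The same section adds: "Two investigators will review each transcript to ensure we establish the reliability of the information extracted". The investigators are also to "discuss conclusions and meanings of unclear messages in the team meetings". Only after that do two people merge the summaries, and the interviewers then check the merged result.

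On who is interviewed, *Inclusion and exclusion criteria* says: "To be eligible for IDIs, participants must self-disclose living with HIV". *Sampling and recruitment* plans 20 such YGBMSM interviews. It also plans five focus groups of 8 to 10 YGBMSM of any HIV status. Men who consent are asked to "refer other YGBMSM known to them". A further 20 interviews are with nurses trained in earlier projects, who are not selected by HIV status.

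On access, *Data collection* says that recordings are to be "encrypted and uploaded to the team box folder, accessible only to key personnel". *Confidentiality and security of data* promises codes or titles in place of names, and contact details held apart from study data.

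**The concern.** For the YGBMSM, having been interviewed already implies living with HIV. If a fellow participant handles material from a single interview and recognises whose it is, he learns that man's HIV status. The article shows why this matters. *Theoretical Underpinning* says that YGBMSM stigmatise one another over HIV status. The Aim 2 design section (STEP 8) reports tightly connected networks and shared sleeping places. *Strengths and future directions* says that men living with HIV conceal it when HIV-negative peers are recruited. Such a disclosure cannot be undone. Men who foresee it may also hold back what the adaptation needs to hear.

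**Working it through.** No power, alpha or effect-size calculation applies. The check sets the sections side by side.

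1. **Who can be on the team.** The article does not say which participants are sampled. The Aim 1 sections give this pool, assuming nobody takes part twice:
   - YGBMSM: focus groups 5 × 8 = 40 to 5 × 10 = 50, plus 20 interviewees, so 60 to 70.
   - Civil-society staff: 2 × 8 = 16 to 2 × 10 = 20.
   - Facility staff: 6 × 8 = 48 to 6 × 10 = 60.
   - Trained nurses: 20.
   - Total: 60 + 16 + 48 + 20 = 144 to 70 + 20 + 60 + 20 = 170.

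   YGBMSM are 60/144 = 42% to 70/170 = 41% of the pool. This is not the chance of selection, but it shows that YGBMSM membership is possible under the text and nowhere excluded. *ADAPT-ITT, Step 2 (Decision)* invites YGBMSM participants to the next team, so their presence here is a natural reading.

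2. **At what stage they work.** The order is team review and summaries, then discussion of unclear points in team meetings, then merging of the summaries, then a check by the interviewers. Participant members therefore act before pooling, while accounts are still separate and most recognisable.

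3. **What recognition would reveal.** All 20 YGBMSM interviewees have disclosed HIV as a condition of entry, so recognising one of them discloses his status in every case. The 20 nurse interviews carry no such implication. The interviews concerned are 20 of 20 + 20 = 40, or half of those planned in Aim 1.

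4. **Whether recognition is plausible.** Recruitment is by venue and by referral among men who know each other, in networks the article itself calls close. It gives no rate of recognition, and none can be derived.

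5. **What the safeguards cover.** Codes, IDs and separate contact details remove the name. They do not remove personal detail from an account that an acquaintance reads or hears discussed. The key-personnel limit is written for recordings, and the term is not defined.

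6. **Follow-up.** Aim 2 *Sampling and recruitment* plans 20 more interviews with YGBMSM living with HIV. Aim 2 *Data analysis* says the Aim 1 process will be reused, but Aim 1 has two. Participants sit on the team only in the adaptation process. The manuscript process lists investigators and the GBMSM+NURSES group, with no participants. The upper limit is 20 interviews if the manuscript process is meant, and 20 + 20 = 40 if the adaptation process is meant.

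**The case against.** A reader might infer that the team's make-up contradicts the key-personnel restriction. The text does not support that. The restriction concerns recordings, each transcript goes to two investigators, and the team's stated subject is key findings. Nothing says that participant members open recordings or transcripts, and key personnel might include the team.

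A reader might also infer that all 20 men will be exposed. Harm needs three things together: a YGBMSM participant on the team, material from a single interview reaching him, and an interviewee he recognises. The article permits each and establishes none. The sampled participants could be nurses or civil-society staff. If they were drawn from the interviewees they too would live with HIV, which softens the concern about HIV-negative peers. It does not remove it, because one man's status would still pass to another without his choice.

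Finally, this is a condensed article with ethics review ahead. Membership rules, confidentiality undertakings and de-identification before team review may be in the full protocol, and involving participants in interpretation is a deliberate choice. That stands, and the absence of such detail is not the point. The point rests on an arrangement the article does state: participants placed on the team at the stage before summaries are merged.

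**Conclusion.** The concern holds as a potential exposure created by a stated arrangement. It is in tension with the access limit on recordings and with the general confidentiality promise, but contradicts neither. Its size is at most the 20 Aim 1 YGBMSM interviewees, plus the 20 at follow-up only if the adaptation process is the one reused. The number of participant members and the chance of recognition are not given, so no expected number of disclosures can be stated.

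The conclusion assumes that YGBMSM participants may be among the team members, which the text allows without saying so, and that summaries or discussion of single interviews reach the whole team. It deserves a change because a disclosure would be irreversible and prevention costs little.

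**What to change.** In the Aim 1 *Data analysis* section, limit recordings, transcripts and single-interview summaries of the YGBMSM interviews to investigators and data collectors. Have participant members comment only on pooled, de-identified themes, after the summaries have been combined. The check of final summaries is now assigned to the interviewers, so participant comment would be added there or left to the Step 2 team, which already includes YGBMSM participants. In Aim 2 *Data analysis*, state which Aim 1 process applies to the follow-up interviews, and apply the same limit if it is the adaptation process.

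The cost is wording and a change in meeting order. The one downside is that participants' input to interpretation comes a step later. *Trail Status* says that recruitment has not begun, so at that point the change could still precede every interview.
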